#### Assessment and treatment of child and mother

At each visit, the clinic assistant will monitor the growth of the child, and screen for maternal depression (PHQ-2 score).^19,20^ Referral will be made to the private GP for further assessment where indicated.

Where indicated, the private GP will assess the child for malnutrition and developmental delay, and the mother for depression using the PHQ-9 score,^19,20^and manage any concerns, including referral to a specialist if necessary.

A logic model and theory of change for the intervention is described in Box 2, drawing on the refined Theoretical Domains Framework.^21^

**Box 2. B2:** Logic model for proposed intervention mechanisms/theory of change (adapted from Bonell and colleagues 2015)^38^

	**Inputs**	**Processes and actions**	**Intended changes (Theoretical domains framework)^21^**	**Intended outputs**	**Intended health outcomes**
**Intervention**	Formative research: interviews with providers, mothers, and key stakeholders Consultation with experts to develop technical materials: • Training protocols and manuals • Counselling flipbook • Community advocate leaflets Training of private GPs and clinic assistants: theoretical and practical training	Quarterly counselling sessions for mothers (child development, child nutrition, maternal mental health) Quarterly child growth monitoring Text message/SMS reminders to mothers for quarterly follow-up appointments Assessment and treatment of chid developmental delay (may include referral) Assessment and treatment of maternal depression (may include)	**Mother** Social influences Knowledge Beliefs about consequences Environmental context and resources Reinforcement **Private GP and clinic assistant** Social influences Knowledge Skills Environmental context and resources Social and professional role and identity	**Mother** Mother–child health services are accessible and desirable to mother Increased capability and confidence to support child nutrition and development in the home environment Increased capability and confidence to protect own mental health in the home environment **Private GP and clinic assistant** Motivated and skilled to provide mother–child health services	Reduced developmental delay at 12 months of age (primary outcome) Improved childhood nutrition Reduced maternal depression
**Both intervention and control arms**	DGHS endorsement of intervention and control clinics Identification and orientation of community advocates Growth Monitoring Cards to intervention and control clinics Standard calibrated equipment to intervention and control clinics Supervision of data entry on Growth Monitoring Card by clinic assistant (Field research officer)	Recruitment of mothers by community advocates Vitamin A supplement		Adequate participant recruitment High quality data	

### Public–private partnership

Both intervention and control clinics will be endorsed by the DGHS to advertise the availability of early childhood development care to the community.

### Community advocates

Participation of mother–child pairs in the study will be encouraged by institution-based members of the community (such as the barber shop or grocery store) advocating for clinics, including distributing study leaflets to interested clients.

### Control clinics

Control clinics will continue usual mother–child care. Control clinic staff will receive basic training only, focused on the correct use of study reporting forms, and a general overview of childhood development and maternal health, that is no training in counselling, or in assessment and treatment of mother–child pairs, or provision of flipbook.

Both intervention and control clinics will receive standardised calibrated equipment (digital scales, and infantometer), to ensure quality of study data. Clinic assistants will be instructed to maintain records in kilograms and centimeters, to ensure uniformity in measurements. Intervention and control clinics will receive a small monthly reimbursement, for participation in research activities.

### Outcomes

#### Primary outcome

##### Suspected developmental delay on screening: ASQ-3 score at 12 months

The Ages and Stages Questionnaire 3^rd^ Edition (ASQ-3) is a childhood developmental screening tool.^22^ By assessing across five developmental domains, it identifies children in primary care who are eligible for further assessment. It is intended that the parent completes the questionnaire, after observing the child at home. However, it can be adapted, for example a parent can be assisted if literacy is poor. Translation and cultural adaptation of the questionnaire is also recommended.^23–25^ Internal and external validity trials of ASQ in a range of populations, cultures, and settings report mixed findings.^24,26–30^ The ASQ-3 questionnaire for children aged 12 months is reported to have a sensitivity of 90% and specificity of 87.5%, when compared to equivalent cutoffs using the Battelle Developmental Inventory-II.^31^ A trial of Hindi ASQ-3 questionnaires in a South Asian population of high and low risk children, found an overall sensitivity of 83.3% and specificity of 75.4%.^32^ The ‘home procedure’ was feasible in India when delivered by non-psychologists, under instruction and supervision. Inter-observer reliability was good. Overall internal validity of the questionnaires was also good, but varied at subscale level.^25^

The ASQ-3 questionnaire has been translated into the Urdu language and adapted to local context for this study. ASQ-3 assessors will have a bachelor’s degree in psychology, and receive training and supervision. Assessment will be conducted at 12 months of age, in private GP clinics. The assessor will record: 1) mother’s responses to the ASQ-3 questionnaire, based on recall and any self-initiated observations; and 2) the assessor’s own on-site observations of specific activities during the assessment session, making use of appropriate toys and props. Mother and assessor scores will be analysed separately, and inter-rater agreement assessed. Final ASQ-3 outcome score will be a composite score of mother response and on-site observations.

#### Secondary outcomes

##### Childhood nutrition status: weight (kg, percentile), length (cm, percentile) at 12 months

Each child will be measured for weight and length by the clinic assistant. Measurements will be plotted on a growth chart, and percentiles calculated. The prevalence of underweight and stunting will be calculated.

##### Maternal depression: PHQ-9 score at 12 months

Maternal depression will be assessed at 12 months by administering the PHQ-9 questionnaire, already available in the Urdu language.^33^ PHQ-2 and PHQ-9 are validated screening tools for depression.^19,20^

#### Data management

##### Participant registration and monitoring data

Sociodemographic information will be recorded at participant enrollment. Ongoing clinical data will be collected by the clinic assistant. Completeness of data collection will be checked by a research officer, who will update trial records, kept securely at the research office. Anonymised electronic data will be entered into SPSS Version 20.0, stored on a password protected computer.

##### 12-month outcome data

All mother–child pairs will be invited to a 12-month final outcome assessment visit. Hard copies of outcome assessment forms will be kept securely, and anonymised electronic data inputted into SPSS (version 20.0) for analysis.

#### Analysis

Both individual and cluster level analysis will be conducted according to intention to treat in SPSS version 20.0 and R version 3.2.3 respectively. Intervention and control arms will be compared at baseline to ensure equal distribution of potential confounders like maternal education, the purpose of randomisation. Scores will be calculated for the five domains of developmental delay namely gross motor, fine motor, problem solving, and personal–social using ASQ3. The two arms will be compared for these five domains of development delay at 12 months by independent sample *t*-test adjusting for clustered data, as used by other researchers,^34^ by applying t.test.cluster in Hmisc package in R. Stunting will be measured at end line using WHO Anthro SPSS Macros. The two arms will be compared with respect to stunting by χ^2^ test adjusted for clustering^35^ by applying donner function in aod package in R.^36^ Mother’s mental health condition will be compared across both arms as end line using PHQ-9 scores *t*-test adjusting for clustered data.^34^ A *P*-value <0.05 will be considered significant. Generalised estimating equation (GEE) and generalised linear mixed models (GLMM) will be applied using R packages gee and glmmML respectively in case of residual confounding.^37,38^

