#### Sample size calculation

At least 1056 mother–child pairs will be required (in 16 clusters: 66 mother child pairs per cluster) in each of the intervention and control arms (a total of 2112 mother–child pairs in a total of 32 clusters) to detect a difference of 20% in development delay (assuming 33% suspected development delay^39^ at baseline) at 80% power, 5% level of significance and an intra-class correlation coefficient of 0.15 for maternal education,^13^ allowing for 10% loss to follow-up in each arm.

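### The trial is sized on the proportion of children with suspected developmental delay, but the only comparison written for the primary outcome is a set of t-tests on five domain scores

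*Protocol article*

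**What the plan says.** Three places in the protocol article bear on the primary outcome.

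- **Primary outcome.** The heading is "Suspected developmental delay on screening: ASQ-3 score at 12 months", which names a yes/no status and a score together. Two raters contribute: "Mother and assessor scores will be analysed separately, and inter-rater agreement assessed". The section then settles which score counts: "Final ASQ-3 outcome score will be a composite score of mother response and on-site observations".
- **Sample size calculation.** There are 1056 pairs per arm (16 clusters of 66), "to detect a difference of 20% in development delay (assuming 33% suspected development delay" at baseline), with 80% power, 5% significance, an intra-class correlation of 0.15 and 10% loss to follow-up. No standard deviation and no score difference is given.
- **Analysis.** Scores are computed for "five domains of developmental delay namely gross motor, fine motor, problem solving, and personal–social using ASQ3". Then: "The two arms will be compared for these five domains of development delay at 12 months by independent sample" t-test adjusted for clustered data, with the R function named. A cluster-adjusted chi-square is assigned to stunting. GEE and GLMM are held for residual confounding and, under Randomisation, for imbalance in clinic size. The only threshold is a P-"value <0.05 will be considered significant".

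**The concern.** The sample size and the analysis answer different questions. One asks whether fewer children screen positive for delay. The other asks whether mean scores differ, separately in each domain. A shift in a mean domain score need not change the proportion below a cut-off, and the reverse can also happen.

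Two consequences follow. First, the 1056 per arm says nothing about the tests that will be run, and the hypothesis it does support is not tested. Second, several tests share one 5% threshold, with no primary domain, no overall score and no rule for what counts as success. A result with one significant domain and four null ones could be reported as reduced developmental delay. That matters because the article ties scale-up to the trial showing effectiveness.

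**Working it through.** **1. What the stated sample size supports.** Inputs from the Sample size calculation: 33%, a difference of 20%, 80% power, 5% significance (two-sided assumed), ICC 0.15, 16 clusters of 66 per arm and 10% loss, leaving 59.4 per cluster (about 60).

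Per-arm n without clustering = [1.96·√(2p̄(1−p̄)) + 0.84·√(p₁(1−p₁)+p₂(1−p₂))]² / (p₁−p₂)². Multiply by the design effect 1 + (m−1)·0.15, then divide by 0.9 for loss.

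| Reading of 20% | n | Design effect (m = 60) | Per arm | After loss |
|---|---|---|---|---|
| 33% vs 53% | 96 | 9.85 | 946 | 1051 |
| 33% vs 13% | 69 | 9.85 | 680 | 756 |
| 33% vs 26.4% (relative 20%) | 752 | 9.85 | 7407 | about 8,230 |

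The stated figure reproduces as a comparison of proportions 20 points apart: 946/60 = 15.8, so 16 clusters, and 16 × 60 × 1.1 = 1056. It does so only with 53% as the second rate, which is an increase, although the aim is a reduction. On any of these readings the quantity sized is a proportion.

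**2. Is that proportion tested?** The written comparisons are:

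- domain scores: clustered t-test;
- stunting: clustered chi-square;
- PHQ-9 scores: clustered t-test;
- GEE/GLMM: for residual confounding, with no outcome named.

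None is a comparison of the proportion with suspected delay. The composite does not close the gap, because it combines mother and assessor, not the five domains.

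**3. False-positive rate if any one domain counts as success.** For five independent tests at 0.05: 1 − 0.95⁵ = 0.226. For correlated tests, take Zⱼ = √ρ·C + √(1−ρ)·Eⱼ with C and Eⱼ independent standard normal, and find the probability that at least one |Zⱼ| exceeds 1.96. The correlation ρ is an assumption.

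| ρ | 0 | 0.3 | 0.5 | 0.7 | 0.8 | 0.9 |
|---|---|---|---|---|---|---|
| Five domains | 22.6% | 20.9% | 18.3% | 14.8% | 12.7% | 10.2% |

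With only the four named domains the rate is 18.5% if independent and 15.6% at ρ = 0.5.

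**4. Power of a single test of the proportion.** Analysed per arm: 16 × 59.4 = 950.4. Design effect: 1 + 58.4 × 0.15 = 9.76. Effective n: 950.4/9.76 = 97.4.

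Power = Φ{[d·√97.4 − 1.96·√(2p̄(1−p̄))] / √(p₁(1−p₁)+p₂(1−p₂))}, where d is the difference.

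- 33% vs 13%: (1.974 − 1.166)/0.578 = 1.40, power 91.9%.
- 33% vs 26.4%: (0.651 − 1.267)/0.645 = −0.95, power 17.0%.

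**5. What the score tests could detect.** At 80% power and 0.05: (1.96 + 0.84)·√(2/97.4) = 0.40 SD per domain. This assumes that ICC 0.15 also holds for the scores, which the article does not say.

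**The case against.** This is a condensed article, and an analysis plan that is not shown may hold the multiplicity rule, the order of domains and the ASQ-3 cut-off. That stands: the absence of a correction is not a finding on its own. It does not remove the mismatch, because the Analysis section goes down to the R function and the comparison it fixes is not the one the trial was sized for. A later plan would have to override or add to it.

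The outcome heading also mentions a score, so analysing scores is not foreign to it. That is fair, but on that reading the sample size calculation loses its link to the primary outcome.

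A reader might infer three stronger things that the document does not support:

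- **That the false-positive rate simply is 15% to 23%.** It depends on an any-domain success rule that the article does not state. Requiring all five domains would keep the rate at or below 5%. The 15% end is not a floor either, since correlations of 0.8 to 0.9 give 10% to 13%.
- **That mother, assessor and composite scores in five domains make 15 primary comparisons.** The Primary outcome section fixes the composite as the outcome, and the Analysis section plans no between-arm test by rater. The separate rater analyses read at least as naturally as agreement work.
- **That the score tests lack power.** What is missing is a power statement. About 0.40 SD per domain may be detectable.

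Naming four of five domains is in itself a drafting slip. It matters here because it leaves the set of tests incompletely defined.

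**Conclusion.** The concern holds as a mismatch within the document. The proportion with suspected delay is what the trial was sized on, and it has no planned comparison. The tests that are planned for the primary outcome have no power statement and no stated success rule. The mismatch needs no assumption, because it follows from setting the three sections side by side.

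The error rate is conditional. It is about 10% to 23% instead of 5% if any single significant domain is taken as success, over assumed equal correlations from 0.9 to 0. The power figures use a normal approximation, two-sided 5%, equal clusters and the ICC of 0.15, which the article quotes for maternal education and not for delay.

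**What to change.** - **Analysis.** Name one primary test: the proportion of children with suspected delay on the mother–assessor composite score, compared once between arms at 5%. Use the cluster-adjusted chi-square already planned for stunting, or a matching GEE/GLMM. State, or point to, the rule that turns the composite into a yes/no status.
- **Analysis.** Make the five domain-score comparisons secondary and list all five domains.
- **Sample size calculation.** State whether the 20% is absolute or relative and in which direction, and restate the power to match: about 92% for 33% versus 13%, about 17% for a relative 20%.

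The cost is wording in two sections and no new data. Domain results lose primary status. If a relative 20% was intended, the clarification will show that the present size falls far short of 80% power, and wording alone will not cure that.

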## Method

### Study design

Pragmatic, parallel arm, clustered randomised controlled trial with two arms (intervention and control) will be conducted to compare an early child development intervention delivered in private urban GP clinics in Pakistan, with usual routine care. Thirty-two clusters will be randomised using a 1:1 ratio, to intervention or control Figure 1.

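### If adjustment is triggered, both GEE and GLMM are applied to 32 clusters with neither named as leading; with uncorrected large-sample tests, those adjusted results run at about 7% rather than 5%, and at 8-9% if either may be cited

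*Protocol article*

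**What the plan says.** The Study design section fixes the number of independent units: "Thirty-two clusters will be randomised using a 1:1 ratio, to intervention or control". The Sample size calculation section gives 16 clusters of 66 pairs in each arm, with 10% loss allowed for.

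The Analysis section first gives each outcome its own test. These are cluster-adjusted t-tests for the ASQ-3 domain scores and the PHQ-9, and a cluster-adjusted chi-square for stunting, obtained "by applying donner function in aod package in R". The significance criterion follows: a P "value <0.05 will be considered significant". Only then does the section add that "Generalised estimating equation (GEE) and generalised linear mixed models (GLMM) will be applied using R packages gee and glmmML respectively", on condition that residual confounding is present. The Randomisation section adds clinic size to both models if the arms turn out unequal on it.

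The Analysis section also states that "Both individual and cluster level analysis will be conducted according to intention to treat", without ranking the two levels. The article does not say which of GEE and GLMM supplies the adjusted result, and it mentions no small-sample correction or degrees of freedom for either.

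**The concern.** Two separate matters meet in one sentence of the plan.

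- **Small number of clusters.** The usual robust (sandwich) variance in GEE is too small with 32 clusters, and more so once cluster-level covariates such as clinic size are added. A mixed model fitted by maximum likelihood with a Wald z test has the same weakness. Intervals come out too narrow in the analyses meant to deal with imbalance.
- **Two unranked models.** If they disagree about the 5% line, nothing in the text says which one is reported as the adjusted finding.

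The adjusted results may well be needed. Allocation is by simple unstratified drawing of 32 clinics, so chance imbalance in clinic size is plausible, and the trigger for adjusting has no stated threshold.

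**Working it through.** **Inputs from the article.** 32 clusters, 16 per arm. Cluster size 66, so 66 × 0.9 = 59.4, taken as 59 analysed. Prevalence 33%. ICC 0.15 (given there for maternal education). Nominal level 5%, the only error rate stated.

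**Assumptions.** Two-sided testing; no small-sample correction; z reference; 0 to 4 cluster-level covariates (the article names one, clinic size); coefficient of variation (CV) of cluster size 0 to 0.6.

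**Step 1, analytic.** For a comparison between clusters with q cluster-level covariates, an uncorrected variance in effect divides the residual sum of squares by 32 instead of 30 − q. The z test then rejects when |t| on 30 − q df exceeds 1.96 × √((30 − q)/32).

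| q | Critical value | Type I error |
|---|---|---|
| 0 | 1.96 × √(30/32) = 1.898 | 6.7% |
| 1 | 1.96 × √(29/32) = 1.866 | 7.2% |
| 2 | 1.96 × √(28/32) = 1.833 | 7.7% |
| 3 | 1.96 × √(27/32) = 1.800 | 8.3% |
| 4 | 1.96 × √(26/32) = 1.767 | 8.9% |

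**Step 2, GEE by simulation.** Null beta-binomial data with the inputs above, 40,000 replicates per cell, exchangeable weights at the true ICC, CV of cluster size 0 and 0.4. The corrected columns use a t reference on 30 − q df.

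| q | Uncorrected z | Kauermann-Carroll, t | Mancl-DeRouen, t |
|---|---|---|---|
| 0 | 6.6-7.1% | 4.7-5.3% | 4.1-4.6% |
| 1 | 7.2-7.3% | 5.0-5.1% | 3.9-4.1% |
| 3 | 8.4-8.8% | 5.1-5.3% | 3.4% |

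**Step 3, both models on the same data.** Logit GEE with robust z and random-intercept logistic ML with Wald z, 4,000 replicates per scenario (Monte Carlo error about 0.4 points).

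| Cluster covariates | GEE | GLMM | Either significant |
|---|---|---|---|
| 0 | 6.8% | 7.1% | 8.0% |
| 2 | 7.3-8.3% | 7.2-7.9% | 8.5-9.2% |
| 4 | 10.1% | 8.8% | 11.2% |

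With Kauermann-Carroll GEE on t, size was 4.8-5.4% throughout. GLMM with a t reference still rejected in 5.9-7.6%. Citing whichever of these two t-referenced models was significant still gave 6.4-8.0%, so a small-sample reference alone does not remove the need to name one.

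**Step 4, the tests outside the adjusted models.** In the same runs a cluster-level t-test rejected in 4.8-5.3% and the Donner chi-square in 6.0-6.4%. A separate set of 20,000 replicates gave 5.6-6.0% for the chi-square.

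**Step 5, what the two models estimate.** For a binary outcome with a logit link, ICC 0.15 corresponds to a random-intercept variance of (π²/3) × 0.15/0.85 = 0.58. The marginal log odds ratio is then about 1/√(1 + 0.346 × 0.58) = 0.91 of the cluster-specific one. For mean scores with an identity link, both models target the same difference.

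**The case against.** The strongest reply is that GEE and GLMM are conditional and come after the named tests. That stands. A reader might infer that the trial's 5% tests in general run at 7-9% or near 10%. The documents do not support this, because the ASQ-3 and PHQ-9 comparisons are cluster-adjusted t-tests and the stunting test is only about one point high.

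A second reply is that a variance correction is a detail an article may leave to the analysis plan, which is not shown. This also stands in part. The inflation figures are conditional on no correction being used, and the article's silence is not a decision against one. The unranked pair of models is firmer ground, because the text commits to both.

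Third, a reader might infer that the differing estimands themselves inflate the error. They do not. Under the null both odds ratios equal 1, and the difference arises only for binary outcomes. The 9% gap on the log scale is a matter of interpretation.

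Fourth, the higher rates need assumptions beyond the text. The article names one cluster-level covariate, and maternal education is an individual characteristic. Rates of 8-9% for a single model need about three cluster-level covariates, and rates near or above 10% need four, or a choice among several analyses, which the article does not propose.

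**Conclusion.** The point holds for the adjusted analyses only. With 32 clusters and uncorrected large-sample tests, their type I error is about 6.7-7.3% with no or one cluster-level covariate and about 8-9% with three. It is about 8-9% if either model may be cited with up to two covariates. The chi-square for stunting, at about 6%, needs no change on this account.

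The size rests on four assumptions: no correction, a z reference, two-sided testing, and the article's own ICC and prevalence. Lowering the ICC to 0.05 made little difference (GEE 8.3%, GLMM 7.9% with two covariates and CV 0.4). The lack of a lead model rests on the text as published. The change should be made, because these are the results a reader would turn to if the arms are unbalanced.

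**What to change.** Before any analysis by arm, name one adjusted model for each outcome:

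- GEE with exchangeable correlation and a Kauermann-Carroll or Mancl-DeRouen variance.
- A t reference with df equal to 32 minus the number of cluster-level parameters: 30 with arm only, 29 with clinic size added.
- GLMM reported as a sensitivity analysis, noting that for a binary outcome its odds ratio is cluster-specific.

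In Step 2, Kauermann-Carroll stayed close to 5% and Mancl-DeRouen was somewhat conservative. One set of runs put corrected GEE at 5.9% when the CV of cluster size reached 0.6, so cluster sizes should be reported.

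The cost is one sentence and a few lines of code. By the approximation in Step 1, intervals widen by about (2.042/1.96) × √(32/30) = 1.08 with arm only, that is 8%, and by (2.045/1.96) × √(32/29) = 1.10 with clinic size added. Replacing the stunting chi-square with a t-test on clinic proportions (30 df) or the same corrected GEE is optional.
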